## Abstract

**Background:**

Major depressive disorder (MDD) is a leading cause of disability worldwide across domains of health and cognition, affecting overall quality of life. Approximately one third of individuals with depression do not fully respond to treatments (e.g., conventional antidepressants, psychotherapy) and alternative strategies are needed. Recent early phase trials suggest psilocybin may be a safe and efficacious intervention with rapid-acting antidepressant properties. Psilocybin is thought to exert therapeutic benefits by altering brain network connectivity and inducing neuroplastic changes that endure for weeks post-treatment. Although early clinical results are encouraging, psilocybin’s acute neurobiological effects on neuroplasticity have not been fully investigated. We aim to examine for the first time how psilocybin acutely (intraday) and subacutely (weeks) alters functional brain networks implicated in depression.

**Methods:**

Fifty participants diagnosed with MDD or persistent depressive disorder (PDD) will be recruited from a tertiary mood disorders clinic and undergo 1:1 randomization into either an experimental or control arm. Participants will be given either 25 mg psilocybin or 25 mg microcrystalline cellulose (MCC) placebo for the first treatment. Three weeks later, those in the control arm will transition to receiving 25 mg psilocybin. We will investigate whether treatments are associated with changes in arterial spin labelling and blood oxygenation level-dependent contrast neuroimaging assessments at acute and subacute timepoints. Primary outcomes include testing whether psilocybin demonstrates acute changes in (1) cerebral blood flow and (2) functional brain activity in networks associated with mood regulation and depression when compared to placebo, along with changes in MADRS score over time compared to placebo. Secondary outcomes include changes across complementary clinical psychiatric, cognitive, and functional scales from baseline to final follow-up. Serum peripheral neurotrophic and inflammatory biomarkers will be collected at baseline and follow-up to examine relationships with clinical response, and neuroimaging measures.

**Discussion:**

This study will investigate the acute and additive subacute neuroplastic effects of psilocybin on brain networks affected by depression using advanced serial neuroimaging methods. Results will improve our understanding of psilocybin’s antidepressant mechanisms versus placebo response and whether biological measures of brain function can provide early predictors of treatment response.

**Trial registration:**

ClinicalTrials.gov Identifier: NCT06072898. Registered on 6 October 2023.

**Supplementary Information:**

The online version contains supplementary material available at 10.1186/s13063-024-08268-6.

## Administrative information

Note: the numbers in curly brackets in this protocol refer to SPIRIT checklist item numbers. The order of the items has been modified to group similar items (see http://www.equator-network.org/reporting-guidelines/spirit-2013-statement-defining-standard-protocol-items-for-clinical-trials/).

## Introduction

### Background and rationale {6a}

Major depressive disorder (MDD) is a leading cause of global disability [1] with individuals facing a relative risk of all-cause mortality 1.7 times greater than the general population [2]. This heterogenous disorder is characterized by episodes of low mood and/or anhedonia, varying in severity and duration, accompanied by a spectrum of symptoms that include psychomotor changes, concentration difficulty, neurovegetative symptoms, suicidal ideation, and impaired functioning [3, 4]. MDD pathogenic effects on large-scale brain networks and alterations in functional connectivity [5–12] is an advancing area of study. Typical treatments include pharmacotherapy, psychotherapy, and therapeutic brain stimulation [13]. Conventional antidepressants (i.e., SSRIs, SNRIs) normalize functional connectivity in key emotion regulation regions [5] and act on glutamatergic and serotonergic neurotransmission [14] to improve executive function [15]. However, those with MDD who are treated with conventional antidepressants experience low remission rates (around 20–42%), a higher incidence of side effects, daily administration, and a delayed therapeutic response that can span weeks [16–20]. This underscores the need to identify alternative antidepressant therapies and to explore new potential mechanisms of antidepressant action.

Psychedelics, particularly psilocybin, are emerging as a promising antidepressant alternative and, at the time of writing, there were > 30 registered clinical studies investigating the safety and efficacy of psilocybin to treat MDD alone. Phase II clinical trials demonstrate that psilocybin is an effective antidepressant comparable to, or even potentially superior to, conventional antidepressants with encouraging results in clinical trials [16, 21–23]. Previous studies have emphasized the lasting antidepressant effects of acute psilocybin treatment with psychotherapy [4, 24], demonstrating both rapid (within days) and enduring (up to 3 months) effects [25, 26], accompanied by alterations in select brain networks for days to weeks [27]. It also exhibits a well-established safety profile with low toxicity and dependence potential [28–30]. Specifically, psilocybin has been shown to induce acute changes in cerebral blood flow (CBF) when measured acutely with arterial spin labelling (ASL) after psilocybin exposure in healthy adults [31, 32], particularly in regions associated with the default-mode network (DMN) [33]. Modulation in the DMN, a network of interconnected brain regions active during resting states and self-referential processes [34], is implicated in MDD, characterized by a global elevation in DMN resting state functional connectivity [35]. In particular, CBF reductions have been found in DMN hubs, such as the posterior cingulate cortex (PCC) and medial prefrontal cortex (mPFC) [33], occurring within hours of psilocybin macro-dosing. As such, it is pertinent to examine DMN regions to characterize regional, group, and session effects associated with psilocybin treatment.

The neurobiological mechanisms underpinning psilocybin’s antidepressant response remain unclear but likely involve changes in neuroplasticity at both cellular [36, 37] and connectomic level [37–39]. In this context, *neuroplasticity* refers to the brain’s ability to adapt structurally and functionally in response to psilocybin [40–42]. Previous research in MDD suggests increased dynamic functional activity and neural flexibility measured by BOLD-fMRI and magnetic resonance spectroscopy [43] during the subacute treatment phase (days to weeks post-dosing). However, the acute effects (e.g., < 24 h post-dosing) of psilocybin-evoked neuroplasticity in MDD remain unknown. Moreover, psilocybin’s agonism at serotonin 5-hydroxytryptamine (5-HT) receptors and its role as a glutamatergic agent are implicated in its neuroplastic mechanisms [44–47] and psychological phenomena such as ego dissolution (i.e., the subjective experience of a breakdown in one’s sense of self and separation between oneself and the world) [43, 48, 49], dream state-like cognitive processing [12, 49], and putative molecular antidepressant mechanisms [36, 50–52].

Placebo effects are well-documented in conventional antidepressant trials in the absence of acute treatment effects [53, 54]. Spontaneous remission of untreated MDD symptoms can occur for many reasons but may take longer compared to antidepressant treatments [55–57]. A recent phase 2 trial comparing psilocybin to an active placebo alongside supportive psychotherapy found significant benefits of psilocybin over placebo on Montgomery-Åsberg Depression Rating Scale (MADRS) and Sheehan Disability Score measures up to 6 weeks post-treatment [58]. However, no difference in MADRS was found at 2 days post-treatment, suggesting psilocybin’s neurobiological effects occur before symptom improvement. This underscores the need to investigate acute brain network changes during psilocybin treatment versus placebo to better understand how psilocybin immediately alters functional connectivity and the neurophysiological mechanisms linked to mood changes in MDD. This exploration may aid in identifying early treatment response markers [54]. For this study, the “acute” timeline will denote any changes that manifest on the day of psilocybin treatment, whereas the “subacute” timeline will encompass any change that occur during the subsequent weeks of follow-up.

Functional neuroimaging is ideal for assessing the acute and subacute effects of psilocybin therapy due to its ability to track changes in brain regions and circuits over treatment. Non-invasive imaging approaches like BOLD contrast and ASL provide reliable whole-brain measures without the need for intravenous contrast agents [59, 60]. BOLD and ASL image contrast share similar information to gold-standard invasive positron emission tomography approaches [61, 62], limiting the need for more costly exogeneous radiotracers. ASL-CBF imaging, offering quantitative maps in mL/100 g tissue/min, is chosen for its excellent temporal and spatial resolution for a cerebrovascular target engagement [63]. The expectation is that the effect of psilocybin on regional CBF will supersede the minimal detectable changes in an ASL assessment that is approximately 10 mL/100 g tissue/min for short and longer time spans [64, 65]. ASL-CBF also allows for easier inter-session comparison compared to fMRI [66]. Despite this, there are no studies examining *acute* fMRI or CBF changes immediately following psilocybin administration in MDD. Previous studies conducted by Carhart-Harris et al. [22], as well as Daws et al. [27], stand as sole published works, to our knowledge, examining neuroimaging differences between psilocybin, placebo, and escitalopram in MDD and TRD, respectively, at a *subacute *(i.e., one day after treatment) timepoint.

Blood-based biomarkers can predict diagnosis, response to medications, and elucidate psychedelic therapeutic mechanisms of action. For example, circulating levels of brain-derived neurotrophic factor (BDNF) are decreased in depression and may be altered by psychedelics [38, 39, 67]. Psilocybin’s antidepressant mechanisms may involve BDNF signalling [68], where levels of BDNF are reduced in healthy individuals after receiving psilocybin [69]. Research that examines changes in the presence of BDNF after psilocybin administration may help to confirm its mechanistic role in MDD and in observed neuroplastic changes measured by neuroimaging. C-reactive protein (CRP), an acute-phase reactant that reflects inflammation, is associated with depression severity and response to other rapid-acting antidepressants [70–72]. Elevated CRP levels are associated with depression [70], with capacity to indicate the presence of chronic inflammation [73, 74]. Furthermore, S100 Calcium Binding Protein B (S100B) is increased in MDD and is associated with glial pathology [67]. Assessing changes in S100B post-psilocybin might be important for determining psilocybin’s effect on MDD-related glial pathology. Integrating neuroimaging with blood biomarkers post-psilocybin in MDD remains unexplored and is vital for understanding acute neuroplastic effects and identifying biomarkers of treatment response.

### Objectives {7}

Our primary objective is to test whether psilocybin (prior to adjunctive psychotherapy) leads to significant acute and subacute changes in functional brain activity in networks associated with mood regulation and depression compared to placebo and supportive therapy. We hypothesize that regional CBF will be modulated during the acute phase of treatment relative to placebo, particularly in brain networks associated with mood regulation and depression. Specifically, there will be an acute increase in dorsolateral prefrontal cortex blood flow and a reduction in the subgenual anterior cingulate cortex blood flow between baseline and the first active treatment (Treatment Visit 1). The CBF findings will be contrasted against resting-state fMRI data. Our secondary objective is to examine whether participants treated with psilocybin-assisted psychotherapy will have a greater reduction in depression scores over time signified by the MADRS relative to those who receive placebo. Our secondary hypothesis is that a reduction in MADRS score will be related to an increase in dorsolateral prefrontal cortex blood flow and a decrease in subgenual anterior cingulate cortex blood flow between baseline and the first treatment visit among participants treated with psilocybin compared to placebo. Additionally, our exploratory objective will examine blood biomarkers that are mechanistically related to psilocybin and/or MDD including those involved with increased neurogenesis and neuroplasticity (BDNF), glial pathology (S100B), and systemic inflammation (CRP). It is predicted that these biomarkers will be associated with MADRS scores at baseline. Our exploratory hypothesis is that our baseline blood-based biomarkers of interest will predict treatment response (i.e., changes in depression scores) measured over time by the MADRS. It is expected that there will be a post-treatment increase in BDNF and a reduction in CRP and S100B plasma levels.

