### Outcomes {12}

Exploratory imaging analysis will consist of voxel-wise analyses to fully characterize regional group and session effects. These analyses will probe circuit-based perspectives by considering the following four relevant resting-state networks: (1) salience, (2) left frontoparietal, (3) right frontoparietal, (4) default mode brain regions. Furthermore, we will conduct brain and behavioural responses, namely regional CBF changes in relation to the MADRS scores. Well-validated markers of brain neuroplasticity (BDNF), systemic inflammation (CRP), and glial pathology (S100B) will be measured in blood at baseline and subsequently evaluated as predictors of treatment response.

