## Data collection and management

### Plans for assessment and collection of outcomes {18a}

The assessments to be collected for both primary and secondary outcomes can be found in Table 2. For each participant, much of the data will be securely stored in the form of an electronic case report form (eCRF) which will include participant demographics, clinical scales and assessments, medical information including any pre-existing conditions and history, concomitant medications and therapies, vital signs (i.e., ECG, blood pressure), baseline blood tests, follow-up visits, any AEs or SAEs (if applicable), documentation of a participant’s informed consent, study visit dates, participant identification numbers, and any documentation pertaining to the appropriate data entry, management, validation, and archival. Paper-based copies of study questionnaires will be kept in the physical CRF with the unique, anonymized identification number assigned to a given participant and securely stored on-site in an area with restricted access at the hospital. Participant data captured during the trial will only be identified by a participant ID and managed in the electronic CRF (eCRF) that will be securely stored in online Research Electronic Data Capture (REDCap) software. REDCap is a secure, web-based software that is designed to support data capture for clinical trials and research studies. MRI data will be stored on a secure research server at Sunnybrook Health Sciences Centre. All questionnaires used in the study have been previously published and validated for research and/or clinical use. The ASL and MRI techniques have been previously published and validated.

**Table 2 Tab2:** Primary and secondary outcomes

**Primary outcomes**	• Significant alterations in regional CBF across three a priori brain regions from baseline to treatment visit 1
	• Improvement in depressive symptoms using the Montgomery-Asberg Depression Rating Scale (MADRS) from baseline to week 3 and week 6 following initial psilocybin/placebo administration. Higher scores with respect to the MADRS minimum (0) and maximum (60) values represent a worse treatment outcome [89]

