## Statistical methods

### Statistical methods for primary and secondary outcomes {20a}

The primary and secondary analyses will be conducted at Sunnybrook Health Sciences Centre, using open-source software tools, to the extent it is possible. Image processing will be conducted by a trained individual who will remain blind to the treatment allocation throughout the data analysis period. We propose to analyze our primary outcome using mixed-effects linear regression to measure CBF changes across our regions of interest from Baseline to Treatment Visit 1, as well as MADRS changes from Baseline, Week 3, and Week 6 following administration. A priori CBF regions consist of emotion regulation regions that are disrupted in MDD [109, 110], comprising the dorsolateral prefrontal cortex, salience network regions comprising the insula cortex, and default mode network comprising the parietal precuneus.

We will determine an optimal model for data analysis by fitting the model described in Eq. 1 to data using the *lme4* package in R, as well as additional models adding interaction effects of age, sex, and number of prior failed antidepressant treatments with drug to assess whether demographics or treatment-resistance modify the effect of psilocybin. An optimal model will be selected by comparing models fit by maximum likelihood estimation using a chi-squared test of model deviance. This will provide the added benefit of further robustness against the possibility of model non-convergence. As described in the sample size calculation, marginal means of a Visit x Drug interaction will be estimated using the *emmeans* package in R, and two within-subject contrasts of baseline to treatment visit 1 change in CBF will be calculated as well as a between-subject difference in these contrasts. Sidak’s correction for multiple comparisons will be applied to adjust *p*-values, with the primary outcome measure being the between-subject difference in the change in CBF attributable to psilocybin vs placebo at treatment visit 1.

For our exploratory analysis, peripheral levels of S100B, BDNF, and CRP will be measured using standard enzyme-linked immunosorbent assays or similar multiplexed immunoassay. All data analyses will be performed using SPSS 22.0. Multivariate linear regression analysis will be used to assess the relationship between baseline and change in peripheral biomarker measures and post-treatment change in MADRS scores.

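### MADRS and functional brain activity change rank between sections, and the stated Sidak step for CBF is not said to extend to the three regions or to MADRS

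*Protocol article*

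**What the plan says.** **MADRS.** Objectives {7} makes it secondary: "Our secondary objective is to examine whether participants treated with psilocybin-assisted psychotherapy will have a greater reduction in depression scores over time". Sample size {14} calls it the second hypothesis and gives no power analysis for it. The abstract's Methods paragraph puts it in the sentence that lists primary outcomes: "along with changes in MADRS score over time compared to placebo". Table 2 has it as a primary row at two times: "Improvement in depressive symptoms using the Montgomery-Asberg Depression Rating Scale (MADRS) from baseline to week 3 and week 6 following initial psilocybin/placebo administration". Statistical methods {20a} adds it to the sentence on analysing the primary outcome: "as well as MADRS changes from Baseline, Week 3, and Week 6 following administration". The same section later names only the between-arm CBF contrast as the primary outcome measure.

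**Functional brain activity.** The abstract numbers it as the second primary imaging outcome: "functional brain activity in networks associated with mood regulation and depression when compared to placebo". Objectives {7} builds the primary objective on it. Table 2's primary rows do not contain it. Outcomes {12} places the voxel-wise and resting-state network work lower: "Exploratory imaging analysis will consist of voxel-wise analyses to fully characterize regional group and session effects".

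**CBF.** Sections {14} and {20a} define the primary endpoint as one between-arm difference in change from baseline to Treatment Visit 1. Table 2 and {20a} apply CBF to three a priori regions.

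**Multiplicity.** Section {20a} says "two within-subject contrasts of baseline to treatment visit 1 change in CBF will be calculated as well as a between-subject difference in these contrasts", followed directly by Sidak's correction; {14} has the same sequence. The power simulation in {14} judges the between-arm contrast on corrected p-values at 0.05. The article does not extend the correction to regions, MADRS or BOLD, and gives no testing order or co-primary rule.

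**The concern.** A reader cannot tell from the article which results would count as the trial's primary findings. A later report could present MADRS as primary or as secondary, and functional brain activity as primary or exploratory, and cite the article for either choice.

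The error rate depends on that choice. The stated correction adjusts over two within-arm contrasts that are not endpoints. The other outcomes that some sections call primary have no stated place in the family. If a positive result on any one of them is read as a primary success, the chance of at least one false claim is above 5%.

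**Working it through.** **1. Ranks side by side**

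| Outcome | Abstract | {7} | {12} | {14} | Table 2 | {20a} |
|---|---|---|---|---|---|---|
| CBF, between-arm | primary | primary | – | primary, one contrast | primary, three regions | primary, three regions |
| MADRS | primary | secondary | – | second hypothesis, no power | primary, weeks 3 and 6 | analysed with the primary outcome |
| Functional (BOLD) activity | primary | primary | network analysis exploratory | – | not in primary rows | – |

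The regions differ too. Objectives {7} names the dorsolateral prefrontal cortex and the subgenual anterior cingulate. Section {20a} names the dorsolateral prefrontal cortex, insula and precuneus.

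**2. The plan's own power figure**

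Inputs from {14}: baseline CBF 55 (SD 13), test-retest variability 3%, psilocybin effect 23% (SD 23%) of own baseline, Sidak over three contrasts. Two-sided testing is assumed.

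Per-test level: 1 − 0.95^(1/3) = 0.01695.

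Test: difference in mean change between arms, SE = √(4s²/n), with s² the residual mean square of a random-intercept model on 2(n − 1)(visits − 1) degrees of freedom; 20,000 simulated datasets per cell. The article does not say how the effect behaves across visits, so three variants were run.

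| Variant | n = 15 | n = 20 | n = 25 |
|---|---|---|---|
| Three visits, one effect per subject | 77.9% | 90.8% | 96.8% |
| Two visits | 86.6% | 95.7% | 98.5% |
| Three visits, effect redrawn each visit | 58.2% | 77.9% | 89.4% |

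The first variant makes 20 per group the first grid size above 80%, which agrees with {14}.

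**3. Family-wise error for CBF alone**

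Three regional between-arm tests at 0.01695: 1 − (1 − 0.01695)³ = 5.0% if independent, and 3.1% at correlation 0.9 (simulated). This works only because the number of contrasts equals the number of regions. If the subgenual anterior cingulate made a fourth region at the same level, the figure would be 1 − 0.95^(4/3) = 6.6% under independence.

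**4. Adding MADRS as primary**

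The article gives no level for MADRS; 0.05 at each of weeks 3 and 6 is assumed. Under the global null with independent tests:

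1 − (1 − 0.01695)³ × 0.95² = 1 − 0.95 × 0.9025 = 14.3%.

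With equal correlation inside the CBF set and inside the MADRS set, and the two sets independent (400,000 simulated vectors): 13.9% at 0.3, 13.1% at 0.5, 12.0% at 0.7, 9.9% at 0.9.

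With one MADRS test at 0.05 instead of two: 1 − 0.95 × 0.95 = 9.75% if independent, 7.9% at correlation 0.9.

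**5. Adding BOLD as well**

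One further independent test at 0.05: 1 − 0.857375 × 0.95 = 18.5%.

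**6. What correction costs in CBF power at 25 per arm**

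Sidak over the three regional between-arm contrasts has the same level, 0.01695, so per-region power is unchanged from step 2. Sidak over all five Table 2 tests has level 1 − 0.95^(1/5) = 0.01021, and per-region power is 94.7% (84.1% to 97.7% over the variants).

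**The case against.** The strongest reply is that the CBF part of the plan is sound and that the rest may be settled in an analysis plan not shown here. Much of this stands.

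- A reader might infer that Sidak protects the within-arm contrasts instead of the primary test. It does not: the between-arm contrast is one of the three, and {14} judges it on corrected p-values.
- A reader might infer that CBF error is already inflated. For the three regions in {20a} it is not, as step 3 shows. One contrast in {14} and three regions in Table 2 are also compatible, since the contrast can be computed in each region.
- A reader might infer that correcting over contrasts and regions together (nine tests) takes power below 80%. No section proposes such a family. At 25 per arm its power is about 76–77% only if the effect is redrawn at each visit, a variant that misses the article's own result at 20 per group. It is 91–92% in the variant that best matches that result and 96% with two visits.
- A reader might infer that following {7} throughout would settle the ranks. It would not: {7} never calls BOLD exploratory, and it names a region that {20a} omits.
- The number of MADRS tests and their level are inferred. The article gives a mixed model over baseline, week 3 and week 6, and does not say that success on any single outcome is enough.

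The reply does not remove the contradiction in rank. An analysis plan can define a family, but it cannot agree with the abstract, {7}, {14}, Table 2 and {20a} at once.

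**Conclusion.** The concern holds in a limited form. The rank of MADRS and of functional brain activity is contradictory within the article, and this needs no assumption. The stated correction is adequate for three CBF regions, by coincidence of number, and is not stated to reach MADRS or BOLD.

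If the five Table 2 tests are all primary, family-wise error is about 14% under independence and about 10% at within-set correlation 0.9. Those figures assume the global null, MADRS tested at 0.05 at each of two times, any single success counting, and independence between the CBF and MADRS sets. The excess over 5% comes from the MADRS label (and from BOLD, if primary), not from the CBF analysis. The documents do not support a claim that the planned sample size is too small for CBF on this account.

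**What to change.** Use one ranked outcome list, worded identically in the abstract, {7}, {12}, {14}, Table 2 and {20a}:

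- **Primary:** the between-arm contrast in CBF change from baseline to Treatment Visit 1, in named a priori regions, with Sidak or Holm across those regional contrasts. Report the two within-arm contrasts as descriptive estimates. Reconcile the regions in {7} and {20a} first, because their number sets the correction.
- **Key secondary:** MADRS at week 3, the last time point before both arms receive psilocybin, tested only after CBF success. After that point the arms no longer compare psilocybin with placebo. The alternative is to put MADRS inside the corrected primary family.
- **BOLD:** state its rank once and use it throughout.

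The cost is rewording. With three regions, the CBF threshold and power do not change. MADRS loses its primary label, but it has no power calculation. If MADRS stays primary, correcting over all five tests lowers per-region CBF power at 25 per arm from 96.8% to 94.7% in the variant that best matches the article. MADRS power would remain unknown, because no effect size or SD is given for it.
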